#### Food frequency questionnaire

FFQ estimates of nutrient intake will be used to support the MD score and to compare the intervention and control groups.

#### Qualitative evaluation of the trial

A sample of participants will be contacted by telephone at the end of the trial period for a recorded semi-structured telephone interview by one of the researchers not involved in meeting the participants. The sample will be weighted 2:1 in favour of the intervention group. This interview will address participants’ views regarding the acceptability of the intervention, any concerns and suggestions to improve the trial.

#### Health economics

We are recording the time taken to deliver the intervention, and the frequency and duration of follow-up telephone calls, to assess the feasibility of reporting intervention costs in a subsequent large-scale RCT. Any problems arising in recording this information will be reported. The patterns of researcher/dietitian time usage in the pilot trial will be used to inform the design of the proposed subsequent RCT.

#### Measurement of potential confounders

We are collecting data related to potential confounders such as the baby’s birth weight, sex, socioeconomic status, maternal education level and exposure to smoking during pregnancy. Given the small sample size in this pilot trial, there will be a limit to how many confounders it will be possible to adjust for in the analysis; however, we will be able to describe their distribution in the two groups.

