### Randomisation

Participating women are randomised when visiting the hospital for their dating ultrasound scan. Allocation to the intervention arm or control arm is by restricted randomisation (by site), via pre-randomised sealed envelopes, based on a predetermined random number allocation. This randomisation has been carried out by an independent statistician. Participants are randomised after consent has been obtained and immediately after the first MD questionnaire has been completed. Participants are enrolled for a total of ~6 months (that is, from 12 to 36 weeks of pregnancy).

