#### Measuring the Mediterranean diet score

The MD score is being measured at baseline (around 12 weeks of pregnancy) and at 12 and 24 weeks post baseline MD questionnaire (i.e. approximately weeks 24 and 36 of pregnancy). The number of times participants consume particular food groups in the last week is classified into never, one or two times, or three or more times. For beneficial components (for example, vegetables, legumes, fruits, cereals, fish, dairy products) the frequency scoring is higher than for components considered less beneficial (meat, fast food, confectionery). As our trial involves pregnant women, we assume dairy products to be protective and we will not include alcohol consumption in the score [16]. This is because of the increased requirement for calcium and the fact that alcohol consumption is not recommended in pregnancy. A 3-point increase in MD score on a scale of 22 could equate to potentially moving from a low-quality maternal MD score into the optimal range of MD score based on the study of Chatzi and colleagues [16].

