#### Mediterranean diet score

Analysis of covariance, adjusting for baseline MD score and using a significance level of 5%, will be used to compare the mean change in MD score from baseline to 12 and 24 weeks between the two groups. As this is a pilot study with a small sample size we will only be able to explore any indications of sustained adherence to the MD.

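### Birth weight is named as a potential confounder open to adjustment, but it arises after randomisation and ordinarily after the last Mediterranean diet (MD) score, so it should only be described by arm

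*Protocol article*

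**What the plan says.** Three places in the protocol article bear on covariates.

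- **Measurement of potential confounders** says data are collected on potential confounders, with these examples for the baby and mother: "birth weight, sex, socioeconomic status, maternal education level and exposure to smoking during pregnancy". It adds that, with a small sample, "there will be a limit to how many confounders it will be possible to adjust for in the analysis", and then that "we will be able to describe their distribution in the two groups". No covariate is fixed.
- **Descriptive analysis**, within the statistical analysis plan section, lists birth weight, the baby's gender and socioeconomic factors among the items to be described for each arm.
- **Mediterranean diet score**, in the same section, compares mean change in MD score at 12 and 24 weeks between the arms by "Analysis of covariance, adjusting for baseline MD score". No other covariate is named.

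On timing, Randomisation states: "Participating women are randomised when visiting the hospital for their dating ultrasound scan". It gives the enrolment period as "from 12 to 36 weeks of pregnancy" and says allocation is restricted by site. Measuring the Mediterranean diet score places the two follow-up scores at "approximately weeks 24 and 36 of pregnancy".

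**The concern.** A confounder of a treatment comparison must act on both treatment and outcome. Randomisation breaks the first link, so baseline variables are adjusted for to gain precision or correct chance imbalance. A variable that arises after randomisation may itself be a result of the allocated arm or of the diet. Conditioning on it can remove part of the effect being estimated, or open a non-causal path between arm and outcome.

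Birth weight is such a variable, yet it heads the list of candidates for adjustment. Smoking exposure, defined over the whole pregnancy, may partly be one as well. If an analyst took the list at face value, the estimated effect of the advice on MD score could be distorted, and that estimate is meant to inform a larger trial.

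**Working it through.** **Timing.** Baseline and randomisation are at about week 12, and the last MD score is 24 weeks later: 12 + 24 = week 36. This agrees with the enrolment period in Randomisation. Birth weight exists only at delivery. It always follows randomisation and, except for births before the final visit, follows the last MD score. It can be neither a baseline covariate nor a confounder of the arm comparison.

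**The other listed variables.**
- Socioeconomic status and maternal education are essentially baseline variables.
- The baby's sex is fixed at conception, so adjusting for it would not carry this bias.
- Smoking exposure during pregnancy covers time on both sides of week 12.

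**Possible size of bias.** The documents give no SD for the MD score and no link between diet and birth weight, so the following is illustration on assumed inputs. The true arm effect is set at 3 units, the difference named in Sample size. The assumed SD is 3.39, the value at which two arms of 20 give 80% power at two-sided 5%: 3 / (2.802 × √(2/20)) = 3.39. The assumed baseline-to-follow-up correlation is 0.5.

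*Case 1: MD score affects birth weight.* Let b be the shift in birth weight, in residual SDs, per SD of MD score. Given arm and baseline, the variance of the follow-up score is 1 − 0.5² = 0.75 in SD² units. The squared partial correlation of score and birth weight is r² = 0.75b² / (1 + 0.75b²). The adjusted arm effect is 3(1 − r²) = 3 / (1 + 0.75b²).

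| b | Formula | Simulated, 1,000,000 women |
|---|---|---|
| 0 | 3.00 | 3.00 |
| 0.1 | 3 / 1.0075 = 2.98 | 2.97 |
| 0.2 | 3 / 1.03 = 2.91 | 2.91 |
| 0.3 | 3 / 1.0675 = 2.81 | 2.81 |

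Without birth weight in the model the simulated effect is 3.00 in every row. With no true arm effect, this route gives no bias, since 0 × (1 − r²) = 0.

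*Case 2: arm shifts birth weight directly, and an unmeasured cause affects both birth weight and MD score.* Take a shift of 0.2 residual SD and a cause explaining 20% of the residual variance of each. The coefficient on birth weight is 3.39 × √0.75 × 0.2 = 0.587, so the bias is −0.587 × 0.2 = −0.12. The simulation gives 2.88 for a true effect of 3, and −0.12 under a true null.

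**Room for covariates.** Trial status reports 30 women recruited. With the 20% attrition assumed in Sample size, 30 × 0.8 = 24 complete. A model with intercept, arm, baseline score and site leaves 24 − 4 = 20 residual degrees of freedom. Adding all five listed variables, at one column each, leaves 15.

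**The case against.** A reader might infer that the plan commits to adjusting for birth weight. It does not. The passage gives examples, stresses the limit on adjustment and offers description by group. The analysis plan section already treats birth weight descriptively. That stands, and it makes this a matter of clarification.

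A reader might also infer that the confounder passage contradicts the analysis of covariance. That is too strong. The analysis of covariance names baseline MD score without excluding other covariates, so the sections are unreconciled but not contradictory.

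Nor can it be said that adjustment would bias the result. Bias is zero if neither diet nor arm affects birth weight, and nothing in the documents fixes its size.

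The confounder list may have been meant partly for the biomarker analysis, which relates changes in urinary markers to changes in MD score. That is a non-randomised association, in which smoking or socioeconomic status could matter. This is fair, but birth weight fits poorly there too, because the final urine sample is collected with the last MD score, ordinarily before birth.

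Finally, a protocol article may leave the exact covariate set to a fuller plan, and the data analysis is to be blind to allocation, which reduces the risk of choosing covariates to suit the result. Both points stand. They do not answer the narrower point that the article names a post-randomisation variable as a candidate for adjustment.

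**Conclusion.** The point holds in a limited form. On the article's own timetable, birth weight cannot confound the randomised comparison of MD score and should not be a candidate covariate for it. The same applies to smoking exposure recorded after randomisation.

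Adjusting for birth weight could bias the arm effect. Under the assumed links above, the bias runs from 0 to about −0.2 units on a 3-unit effect. A stronger link would give more, and the documents offer no basis for choosing a value.

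The documents do not support a ban on socioeconomic status or maternal education. These are essentially baseline variables, and the only reservation is how many the sample can carry. The practical impact is modest: MD score is a secondary aim, and the primary aims of recruitment, retention and acceptability are untouched.

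**What to change.** - In Measurement of potential confounders, state that birth weight and any other variable measured after randomisation, including smoking exposure after the dating scan, are described by arm only and are not covariates in the arm comparison. This brings the passage into line with Descriptive analysis.
- In the Mediterranean diet score analysis, limit adjustment to pre-randomisation variables: baseline MD score, as now, plus site. Site is not mentioned there at present. The reason to add it is that Randomisation restricts allocation by site.
- If a further baseline covariate such as socioeconomic status or education is wanted, name it in advance and keep the number very small.

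The cost is a few sentences of text and one degree of freedom for site. Data collection does not change, and all the listed variables can still be reported by arm.

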### Sample size

Our intention is to continue recruitment until we have 50 women included in the trial in order to answer our research questions. Both centres have approximately 100 dating scans per month, but there is seasonal variation. We estimate that at least 800 invitations will be made, and those who do not respond prior to the ultrasound scan appointment have a further opportunity to take part if they respond to the clinic poster. Of the 800+ invitations made, we estimate that one-quarter (*n* = 200) will fulfil the eligibility criteria (‘Do you (the mother), or the father, or sibling of the baby have an allergic disease …?’). This estimate is based on an overall assessment of the epidemiology of allergic disorders in Scotland, systematic reviews of a number of previous primary prevention trials [26,27] and a recent dietary intervention trial in pregnant women [14]. Based on our discussions with consumer representatives that have informed this pilot trial, we anticipate that ~25% (that is, *n* = 50) of eligible women will be willing to take part and, with an estimated 20% attrition/incomplete data collection during the course of the pregnancy, we anticipate that 40 participants will complete the study. If these assumptions are fulfilled, recruitment and retention will be comparable with other leading international primary prevention trials [27].

As this is a pilot trial, using a questionnaire based on Castro-Rodriguez and colleagues [18], we estimate that using a level of 0.05 (two-tailed) and power of 80% will require a sample size of 40 to detect a statistically significant difference in the mean MD score of the intervention group, from baseline, in the order of 3 units.

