## Trial status

At the time of submission, 22 participants had been recruited. At the end of recruitment (December 2012), 30 participants had been recruited.

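### Recruitment ended at 30 against an intended 50, but the 40-completer, 80%-power statement and the 5% test on the Mediterranean diet score were not revisited

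*Protocol article*

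**What the plan says.** The Sample size section sets the target as an intention: "Our intention is to continue recruitment until we have 50 women included in the trial in order to answer our research questions". It reaches that number through a funnel that starts "Of the 800+ invitations made, we estimate that one-quarter" being eligible (200 women), of whom about 25% are expected to agree (50). It continues: "with an estimated 20% attrition/incomplete data collection during the course of the pregnancy, we anticipate that 40 participants will complete the study".

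The same section then gives the power statement: "we estimate that using a level of 0.05 (two-tailed) and power of 80% will require a sample size of 40", the target being a "difference in the mean MD score of the intervention group, from baseline, in the order of 3 units". No SD is given for the score or for its change.

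The analysis plan, under Mediterranean diet score, compares the two groups by "Analysis of covariance, adjusting for baseline MD score and using a significance level of 5" per cent, at 12 and 24 weeks. It adds that, with a small sample, sustained adherence can only be explored.

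Trial status reports: "At the end of recruitment (December 2012), 30 participants had been recruited". The Trial timeline agrees that randomisation ran from June to December 2012. Neither place says why recruitment stopped at 30 or what follows for size or power.

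Under Aims of the study, recruitment, retention and acceptability are primary. Change in MD score is secondary.

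**The concern.** One section ties 80% power to 40 completers, and another shows that 40 completers cannot be reached. The article leaves both standing and still plans a test at the 5% level.

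What is at stake is how the MD-score result will be read. The section on measuring the score treats a 3-point rise on its 22-point scale as possibly enough to move a woman from a low-quality score into the optimal range. If the 3-unit effect is real, a non-significant result is considerably more likely with 24 or 30 women than with 40. A reader who takes the 80% at face value could count such a result as evidence that the advice does not change diet. The Discussion says the pilot serves to refine the intervention and to inform the size of a later trial, so that misreading could carry forward.

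**Working it through.** **Inputs.** From Sample size: intended recruitment 50, attrition or incomplete data 20%, 40 completers, two-sided level 0.05, power 80%, difference 3 units. From Trial status: 30 recruited. Assumed, because the article does not state them: 1:1 allocation, the same 20% loss among the 30, and an SD solved from the plan's own power claim. No gain from baseline adjustment is included, since no correlation is given.

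**Step 1: the plan's funnel.** 800 × 0.25 = 200; 200 × 0.25 = 50; 50 × 0.8 = 40. These figures reproduce exactly.

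**Step 2: what 30 recruits give.** 30/50 = 60% of target. Expected completers are 30 × 0.8 = 24, about 12 per arm. The ceiling is 30, about 15 per arm. Both are below 40.

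**Step 3: the SD implied by 40 giving 80%.** The stated sample size cannot be reproduced directly without an SD. The contrast is also unclear: the power sentence describes change from baseline in the intervention group, while the analysis compares groups. I therefore solved for the SD under three readings, using the noncentral t distribution. The noncentrality is 3/(SD × √(2/n)) for n per arm, or 3/(SD/√n) for a paired change in n women.

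| Reading of the 40 | Implied SD | Power, 24 completers | Power, 30 completers |
|---|---|---|---|
| Two-sample, 20 per arm | 3.30 | 57% (12 per arm) | 67% (15 per arm) |
| Paired change, 40 women | 6.60 | 57% (24 women) | 67% (30 women) |
| Paired change, 20 in the intervention arm | 4.54 | 55% (12 women) | 66% (15 women) |

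Worked example, first row with 12 per arm: noncentrality 3/(3.30 × √(2/12)) = 2.23, critical t on 22 df = 2.07, power 0.567. The loss is nearly the same under all three readings.

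**Step 4: difference detectable with 80% power.** By the normal approximation it scales as 3 × √(40/N): 3 × √(40/24) = 3.87 and 3 × √(40/30) = 3.46. The two-sample t calculation gives 3.95 and 3.50.

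**Step 5: how far absolute power depends on the missing SD.** For a two-sample t-test with 12 per arm and a difference of 3 units:

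| SD | 2.0 | 2.5 | 3.0 | 3.5 | 4.0 | 5.0 |
|---|---|---|---|---|---|---|
| Power | 94% | 80% | 65% | 52% | 42% | 29% |

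Only the fall relative to the plan's own 80% can be supported.

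**Step 6: precision of retention (primary aim).** Exact (Clopper-Pearson) 95% intervals at 80% retention:

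- Overall: 66-90% for 40/50, against 61-92% for 24/30.
- One arm at the achieved size: 52-96% for 12/15.

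The overall interval widens modestly. The by-arm interval is wide.

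**The case against.** The best defence is that this is a target followed by an openly reported outcome. The 50 was an intention, built on estimates and made conditional on assumptions. The requirement of 40 is an a priori statement, and recruiting fewer women does not make it false. The shortfall is disclosed in Trial status. In a pilot whose primary aims include the recruitment rate, 30 against 50 is something the trial was set up to find out. The power sentence serves only a secondary aim, the analysis plan already acknowledges a small sample, and the numbers at each recruitment stage and the retention rate are already to be reported.

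Most of this stands, and it limits the point. It does not remove it. The article discloses the count but not its consequence. The small-sample caveat covers sustained adherence only and withdraws neither the 80% nor the 5% test.

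A reader might infer more than the article supports:

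- *That the sample-size arithmetic is wrong.* The funnel reproduces exactly.
- *That the trial's power is 57%.* That figure depends on a back-solved SD, 1:1 allocation and a projected 24 completers. Absolute power is unknown.
- *That recruitment closed under a date rule.* The article gives the months of randomisation but no such rule and no reason for stopping.
- *That the primary aims are undermined.* Overall retention loses little precision, and the article states no precision target or progression threshold that the wider interval would miss.

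**Conclusion.** The point holds as an unreconciled statement of size and power, of minor to moderate severity. It is not a flaw that must be repaired before the trial can be relied on for its primary aims.

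That 30 recruits cannot give 40 completers needs no assumption. The size of the power loss (80% to about 55-57% with 24 completers, or 66-67% if all 30 complete) takes the plan's claim that 40 gives 80% as true. The 24-completer figure also assumes the planned 20% loss. The conclusion does not depend on which contrast the power sentence meant.

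**What to change.** Leave the a priori target and its reasoning on record. Beside them, state:

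- that 30 women were recruited, and the actual reason recruitment ended, which only the investigators can supply;
- that 40 completers cannot be reached, so the 80% power for 3 units no longer holds. Any new power figure should name the SD, its source and the contrast it refers to.

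In the analysis plan, present the between-group MD-score comparison as an adjusted mean difference with a 95% confidence interval. Draw no claim of effect or of no effect from the 5% test.

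Report 30 recruited against 50 intended as a feasibility outcome in its own right. Give retention overall and by arm with exact 95% intervals.

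The cost is wording only: no extra women and no new data. The stated power and precision become less favourable.

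### The 80% power is stated for a change from baseline within the intervention group, but the planned test of the MD score is a between-arm ANCOVA, so the figure does not attach to that test

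*Protocol article*

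**What the plan says.** The Sample size section works from invitations to recruits and then to completers. It expects 50 women to join, allows 20% for drop-out or missing data, and on that basis says "we anticipate that 40 participants will complete the study". Trial design describes two parallel arms, so this 40 is the whole trial. Randomisation is restricted by site, and no allocation ratio is given.

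The same section then claims 80% power at the two-sided 5% level from 40 women. The effect it names is "a statistically significant difference in the mean MD score of the intervention group, from baseline, in the order of 3 units". This is the only power statement in the article.

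Under Statistical analysis plan, Mediterranean diet score, the only test described is an ANCOVA adjusted for baseline score at the 5% level, which "will be used to compare the mean change in MD score from baseline to 12 and 24 weeks between the two groups".

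Aims of the study places MD score change among the secondary aims. The primary aims are recruitment, retention and acceptability. Trial status reports that recruitment closed at 30.

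**The concern.** The power sentence and the analysis section describe different contrasts. One is the mean change in a single arm against zero. The other is the difference in change between two arms, which has a different standard error for the same number of women. A power figure for the first says nothing definite about the second.

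The sentence also appears to apply the total number of completers to a contrast that uses only one arm. Read literally, with 40 women in the intervention group, a 1:1 trial would need 40 × 2 = 80 completers, and 80/(1 − 0.20) = 100 women randomised, not 50.

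At stake is how the MD score result is read. A colleague who takes the 80% at face value would give a non-significant ANCOVA more weight as evidence of no effect than it may deserve. Estimates of what the later large trial needs could also start from a power claim that was made for another quantity.

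**Working it through.** **Inputs from the document.** Two-sided alpha 0.05, power 80%, difference 3 units and N = 40 (Sample size); between-arm ANCOVA adjusted for baseline (Mediterranean diet score); 20% attrition and target 50 (Sample size); 30 recruited (Trial status).

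**Assumptions.** Allocation is 1:1, so 20 completers per arm. The SD of the score is equal at baseline and follow-up. The SD of change and the baseline/follow-up correlation r are not given, so both are varied.

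**Step 1: the plan's own figures.** Attrition checks: 40/(1 − 0.20) = 50. The N of 40 cannot be reproduced without an SD, so I solve for the SD of change that makes 80% true at 3 units under each reading.

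Normal approximation, with 1.960 + 0.842 = 2.802:
- Paired, 40 women: SD = 3√40/2.802 = 6.77
- Paired, 20 women: SD = 3√20/2.802 = 4.79
- Two groups, 20 per arm: SD = 3/(2.802 × √(2/20)) = 3.39

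The exact noncentral-t values are 6.60, 4.54 and 3.30 (standardised differences 0.454, 0.660 and 0.909). These are used below.

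**Step 2: between-arm power at 3 units with 20 per arm.** For change scores, the noncentrality is 3/(SD × √(2/20)) on 38 df. For ANCOVA, the residual SD is SD × √((1 + r)/2), on 37 df.

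| How the 40 may have been obtained | Implied SD of change | Change scores | ANCOVA, r = 0.7 | ANCOVA, r = 0.3 |
|---|---|---|---|---|
| Paired, 40 women in the arm | 6.60 | 29% | 33% | 41% |
| Paired, 20 women in the arm | 4.54 | 53% | 60% | 71% |
| Two groups, 20 per arm | 3.30 | 80% | 86% | 93% |

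Worked line: for SD 4.54 and r = 0.3, the residual SD is 4.54 × √0.65 = 3.66, the noncentrality is 3/(3.66 × 0.3162) = 2.59, and power is 71%. At r = 0 the residual SD is 4.54 × √0.5 = 3.21 and power reaches 82%.

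**Step 3: detectable between-arm difference at 80% power.**
- 20 per arm, as planned: 0.91 SD. Three units requires an SD of at most 3/0.91 ≈ 3.3.
- 12 per arm, from 30 recruited and 20% lost (30 × 0.80 = 24, halved): about 1.20 SD. Three units requires an SD of at most 3/1.20 = 2.5.

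For ANCOVA, the SD in these two lines is the residual SD after baseline adjustment.

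**The case against.** The strongest reply is that the sentence is a loosely worded two-group calculation. On that reading the implied SD is 3.3, the 80% holds for change scores, and ANCOVA does better. This may be so. The text names the intervention group and baseline, however, and nothing in the article supports the other reading. If it is right, the sentence still needs the same correction.

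A second reply is that this is a pilot, sized from expected recruitment, with the MD score as a secondary aim. That stands and lowers the severity. It does not remove the mismatch, because the authors chose to state a power and a 5% test. Their caution about exploration concerns sustained adherence only.

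A third reply is that change over time is a legitimate question, since the aims mention changes in both groups. It is, but the analysis section gives it no separate test.

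Four stronger readings are tempting, and the documents do not support them:
- *That the trial is shown to be underpowered for the ANCOVA.* The table runs from 29% to 93%, and the document does not say which row applies.
- *That only a two-group calculation could deliver 80%.* The paired calculation with 20 women gives 82% by ANCOVA at r = 0.
- *That the absent SD is itself a fault.* The calculation refers to a cited questionnaire study, and a condensed article may leave the SD to the full protocol.
- *That the plan will draw its conclusion from the intervention arm's rise, inflated by regression to the mean.* The only planned test uses the randomised control. The women are also selected on pregnancy, age and family allergy history, not on MD score.

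**Conclusion.** The point holds as an inconsistency between two stated contrasts. The 80% is attached to a within-arm change, the N is the total for both arms, and the planned test is between arms. No outside figure is needed to see this.

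The size of any loss of power is conditional on an unstated SD and correlation and on an assumed 1:1 ratio. The power of the planned test is therefore not established by the document, at 80% or at any lower figure. Severity is moderate: the primary aims do not depend on this sentence, but the interpretation of the MD score comparison does.

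**What to change.** Replace the power sentence with a between-arm statement that matches the ANCOVA and gives completers per arm, the allocation ratio, the assumed SD with its source, and the detectable difference. Suggested content:

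- As planned, 20 completers per arm give 80% power at two-sided 5% for a between-arm difference of 0.91 SD, which is 3 units only if the SD is about 3.3 or less.
- With 30 recruited and 20% attrition, 12 completers per arm give 80% power for a difference of about 1.20 SD, which is 3 units only if the SD is about 2.5 or less.

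Alternatively, drop the power claim and give the expected precision of the between-arm difference. In either case, state that the between-arm difference will be reported with a confidence interval, and that change from baseline within an arm is descriptive and not evidence of an intervention effect.

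The cost is wording only. Recruitment and the planned analysis are unchanged, although the restated power may be less favourable than 80%.
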